### Outcome measures

#### Primary

*1. Binary composite outcome score*:

Treatment success and failure will be defined at study completion (1 year) using a system of major and minor criteria modified from others [8,14,18] (Figure 4).

**Figure 4 F4:**
[figure not shown]
Binary Composite Primary Outcome Measure.

*2. Ophthalmopathy index *[44]:

Treatment response at study completion (1 year) will also be quantified using the Ophthalmopathy Index (OI) as a continuous measure of disease *severity*.

#### Co-primary

*1. Clinical activity score *[45,46]:

Short-term response to treatment (3 months) will be evaluated using the Clinical Activity Score (CAS, Table 1) as a continuous measure of disease *activity*.

#### Secondary

1. *Clinical measures:*

Total eye score (TES) [6].

2. *Psychosocial measures *[see Additional file 2]:

- Hospital Anxiety and Depression Scale (HADS) score [47]

- Derriford Appearance Scale-Short Form score [48,49]

- Graves' Ophthalmopathy Quality of Life (GO-QoL) score [50,51]

- WHOQoL-Brief Quality of Life Assessment Score [52]

- Open-ended responses to interview questions

3. *Health economic measures *[see Additional file 1]:

The cost of TED and its treatment will be measured from the perspective of the NHS, the patient and society.

#### Adverse events

Adverse events will be documented and serious adverse events will be reported to the trial sponsor and to the Medicines and Healthcare Products Regulatory Agency (MHRA). Specific enquiries regarding known side-effects of the active interventions in the trial (as documented below) will be made at each visit and documented. Clinical examination will include monitoring for adverse events.

*Prednisolone *– gastric irritation/ulceration, weight gain, sleep disturbance, mood

disturbance, increased susceptibility to infection, increase in blood pressure, steroid induced diabetes.

*Azathioprine *– malaise, nausea, vomiting, diarrhoea, rash, myalgia, hair loss, increased susceptibility to infection. Regular blood tests will be carried out on all patients to monitor for bone marrow suppression and liver impairment.

*Radiotherapy *– localized redness of skin, cataracts, radiation retinopathy.

As this is a double-masked trial all adverse events will be documented and reviewed by the data monitoring committee who may be unmasked to treatment allocation.

### Trial size

#### Number of patients

A two group continuity corrected chi-squared test with a 0.050 two-sided significance level will have 80% power to detect the difference between a success rate in the placebo arm of 60% and success rate in the treated arm of 87% (odds ratio of 4.462) when the sample size in each group is 48. It is therefore necessary for there to be 96 subjects with complete final data sets to be equally distributed to the 4 treatment groups.

The power for continuous outcome measures is more favourable and a total sample size of 100 patients will yield 92% power to detect a difference of 2.7 in the OI with two-sided 5% alpha, assuming a standard deviation of 3.3.

CAS is not considered as important as the primary outcomes in terms of influencing future clinical practice. However it is of greater interest and importance than the secondary outcome variables, and as such it has been selected as a coprimary endpoint and the power of the trial to detect a clinically important difference is presented here. Assuming a standard deviation of between 1.2 and 2.0, a total sample of 100 patients will yield between 71% and 99% power to detect a difference of 1 point with 5% two-sided alpha.

The above power calculations are based on comparisons 'at the margins' of the factorial design (ie, comparing all azathioprine treated patients with placebo treated patients, and all radiotherapy treated patients with sham-radiotherapy treated patients). There will be low power for comparisons between individual cells of the factorial design (eg azathioprine and sham-radiotherapy vs. placebo and radiotherapy), although these analyses will still be conducted to generate pilot data on the comparative efficacy of the 4 combination regimes under investigation.

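### The power sentence for the Ophthalmopathy Index is internally inconsistent: its printed inputs give about 98% power, not 92%

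*Protocol article*

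**What the plan says.** The Protocol article names two primary outcomes at one year: a binary composite and the OI as a continuous measure of severity (Outcome measures, Primary).

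Under Trial size, Number of patients, the binary composite is treated first. Success rates of 60% and 87% lead to 48 per group, hence "96 subjects with complete final data sets to be equally distributed to the 4 treatment groups".

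The OI follows: "a total sample size of 100 patients will yield 92% power to detect a difference of 2.7 in the OI with two-sided 5% alpha". For the variability, the sentence takes 3.3 as the standard deviation. The CAS comes next, with 71% to 99% power for a difference of 1 point when the standard deviation lies between 1.2 and 2.0, again with 100 patients.

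The section then states the comparison to which all these figures apply: "The above power calculations are based on comparisons 'at the margins' of the factorial design". It gives no dropout allowance, alpha split or other adjustment for the OI figure.

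**The concern.** The OI sentence prints total size, difference, standard deviation, alpha and power together, so it can be checked on its own terms. A difference of 2.7 against a standard deviation of 3.3 is a standardised effect of about 0.82. That is large for 50 per group, and 92% looks too low for it.

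If the five numbers cannot all be true, a reader cannot be sure that 2.7 and 3.3 are the planning values that were meant. The size of the doubt is as follows:

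- If the inputs are right, the chance of missing a true difference of 2.7 is about 2% rather than 8%.
- If 92% is right and the standard deviation or the difference was misprinted, the intended value differs from the printed one by roughly a fifth.

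**Working it through.** **Inputs** (all from Number of patients)

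- Total 100, compared at the margins with equal allocation to the four cells, so n = 50 per side.
- Difference 2.7, standard deviation 3.3, two-sided alpha 0.05.
- Stated power 92%.

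**Attempt to reproduce the stated figure**

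- Standardised difference: 2.7 / 3.3 = 0.818.
- Noncentrality: 0.818 × √(50/2) = 0.818 × 5 = 4.09.
- Normal approximation: power = Φ(4.09 − 1.96) = Φ(2.13) = 98.3%.
- Noncentral t with 98 degrees of freedom: 98.2%.
- With 48 per side (the 96 complete data sets), noncentral t: 97.8%.

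The stated 92% is not reproduced.

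**Do the other figures in the section reproduce?**

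- CAS, standard deviation 2.0: (1/2.0) × 5 = 2.50; Φ(2.50 − 1.96) = 70.5%, stated as 71%.
- CAS, standard deviation 1.2: (1/1.2) × 5 = 4.17; Φ(4.17 − 1.96) = 98.6%, stated as 99%.
- Binary outcome, 60% against 87%, 80% power, continuity corrected: 47.9, so 48 per group, as stated.
- Odds ratio: (0.87/0.13) / (0.60/0.40) = 4.462, as stated.

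The lower CAS figure matches under the normal approximation; noncentral t gives 69.7%. This choice of method moves the OI result by only 0.1 point.

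**Could an unstated convention explain 92%?** (noncentral t; difference 2.7 and standard deviation 3.3 kept, except in the last row)

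| Variant | Power |
|---|---|
| One-sided 5% | 99.2% |
| 80 residual degrees of freedom after covariate adjustment | 98.1% |
| Rank test, relative efficiency 0.955 / 0.864 | 97.7% / 96.4% |
| 85 patients (the 10% and 5% losses under Compliance and loss to follow-up, summed and applied to everyone) | 96.1% |
| Alpha 0.025 (two primary outcomes) | 96.4% |
| Alpha 0.0125 (two outcomes by two interventions) | 93.7% |
| One cell against the other three, 25 v 75 | 93.9% |
| One cell against another, 25 v 25 | 80.9% |
| Standard deviation × √2 | 81.7% |

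No variant that keeps the marginal comparison, the 5% alpha and the printed standard deviation falls below 96%. The two that come closest to 92% contradict the text: one abandons the stated 5% alpha, the other the stated marginal comparison.

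**What would give 92%, changing one input at a time** (noncentral t)

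- Standard deviation about 3.97 instead of 3.3 (3.97/3.3 = 1.20).
- Difference about 2.24 instead of 2.7 (2.24/2.7 = 0.83).
- About 35 per group instead of 50 (35 gives 92.1%).
- Alpha about 0.01 instead of 0.05 (0.01 gives 92.6%).

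**The case against.** The strongest reply is that nothing in the design depends on this number. The required 96 complete data sets come from the binary composite, and that calculation reproduces. The OI sentence serves only to show that power for continuous outcomes is more favourable than 80%, which is true at 92% and at 98%. If the printed inputs are right, the protocol understates its power. If 92% is right and the difference or the standard deviation was misprinted, power for the intended effect is still 92%. All of this stands, and it limits the point to a correction of the text.

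A reader might go further and infer any of three things that the document does not support:

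- **That the trial is wrongly sized or underpowered for the OI.** Neither way of resolving the inconsistency leads there.
- **That 98% is the true figure and 92% is simply the typing error.** The document shows that the numbers disagree, not which one is wrong.
- **That a non-significant OI result could not be judged against the planned effect.** The Statistical analyses section gives full weight to estimates and confidence intervals. An interval can be set against 2.7 whatever the planned power was. What remains is the narrower doubt whether 2.7 and 3.3 are the values intended.

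The reply does not rescue the figure. The sentence is complete as printed, with no missing figure or broken table in it, and a gap of 6 points is neither rounding nor the choice between z and t.

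**Conclusion.** The point holds as an internal inconsistency. With 50 against 50, a difference of 2.7, a standard deviation of 3.3 and two-sided 5% alpha, power is about 98%, not 92%. At least one of the five printed numbers is wrong, and which one cannot be settled from the document.

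This rests on two readings that the section itself supplies: the comparison is at the margins, and allocation is equal. It also assumes an ordinary two-sample comparison of means with no unstated adjustment. The adjustments tried at the stated alpha, margins and standard deviation still give 96% or more.

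The consequence is modest. Trial size and conduct do not change, and the error is conservative if the inputs are as printed. It is worth correcting because the sentence sets the planned effect and variability for a primary outcome, and those values should be reliable.

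**What to change.** Go back to the original OI calculation and correct the sentence in one of two ways:

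- If the difference of 2.7, the standard deviation of 3.3, the 100 patients and the 5% alpha are as intended, restate the power as about 98%.
- If 92% was the calculated result, correct whichever input (difference, standard deviation, sample size or alpha) was misprinted.

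Naming the method used (normal approximation or t) would let a reader reproduce the OI and CAS figures alike. Stating the difference detectable with 80% power is optional and not needed for the correction.

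The cost is one corrected sentence, with no extra patients and no change to the analysis.

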#### Compliance and loss to follow-up

We predict that 33% of eligible patients will choose not to take part in the study [14], 11% will be excluded because of TPMT inactivity [53], 10% of the azathioprine treated group will be intolerant of therapy or suffer an adverse event necessitating withdrawal from the trial [54], and 5% will drop-out for other reasons.

### Statistical analyses

Data analysis will proceed according to CONSORT guidelines for randomised controlled trials. The first stage of the analysis will be to use descriptive statistics to describe the group of individuals recruited to the trial in relation to those eligible, and to investigate comparability of the trial arms at baseline. The primary intention-to-treat analyses will comprise comparisons between radiotherapy versus sham-radiotherapy, and azathioprine versus placebo, for each of the two primary outcomes at 12 months follow up. The comparisons will be made using appropriate (that is, logistic or linear) multivariable regression models, adjusting for minimisation variables, the factorial design, and the value of the outcome variable at baseline. Full attention will be paid to the estimates and the confidence intervals for these comparisons as well as the p-values. Secondary analyses will then be conducted using regression models with further adjustment for any prognostic factors that exhibit marked imbalance at baseline. Patients who have no outcome data for the primary analyses will have data imputed using last observation carried forward. Patients who have become non-compliant for any reason will still be invited to produce outcome data such that they can be included in the intention to treat analyses. The assumptions required for the regression models will be investigated using appropriate diagnostic plots, and actions such as transformation of continuous outcome variables taken as necessary.

The co-primary outcome CAS at 3 months follow up, and all secondary outcomes, will be analysed in the same way, using appropriate (linear or logistic) regression models depending on the nature of the outcome measure. Bonferroni corrections for multiple testing will be considered for the secondary outcomes.

Other secondary analyses will involve: (a) investigation of any interaction between the two interventions for each of the two primary outcomes; (b) pre-planned sub-group analyses to ascertain any differential effects of the interventions according to steroid use versus no steroid use in the six months prior to enrolment. These secondary analyses are readily performed as extensions to the multivariable regression models described above, by simply introducing the appropriate interaction terms. However, the precision of the estimates of interaction is very likely to be too poor, and high p-values will most likely reflect low power and so cannot be taken as evidence for no interactions.

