### Allocation of trial interventions

Patients who are eligible to continue in the study at the second trial visit (after confirmation of active disease by response to steroids or short disease duration – see above) are allocated to treatment groups by minimisation. This is a dynamic process which reduces the imbalance between trial arms with respect to a range of predefined prognostic variables, and a randomisation schedule is therefore not drawn up in advance. Instead, a form categorising each study recruit according to the minimisation criteria set out in Table 6 is returned to the randomisation service at Moorfields Eye Hospital on enrolment, giving them time to determine the patient's treatment allocation should they be eligible to proceed in the study. The trial pharmacists at each Trial Centre then phone the randomisation service on receipt of a trial IMP prescription at the patient's second visit, and are notified whether they are to dispense azathioprine or placebo. This is confirmed by email, which also states the patient's radiotherapy group – a copy of which is sent to the Trial Radiotherapy Centre radiographers and the un-masked trial co-ordinator.

**Table 6 T6:** Minimisation Criteria

**Minimisation criteria**	**Categories**
Smoker at time of TED diagnosis	Yes/No
Previous Steroid use*	Yes/No
Gender	Male/Female
Disease severity	TES < 22/TES ≥ 22
Study Centre	MEH/BEH/WEH/UCLH/MREH
Disease duration	< 6 months/≥ 6 months
Age	< 60 years old/≥ 60 years old
Disease activity	CAS 2–3/4–5/6–7
Thyroid status on enrolment	Hypothyroid/Euthyroid/Hyperthyroid

* Defined as ≥ 20 mg of prednisolone for ≥ 1 month in the previous 6 months

TES: Total Eye Score; MEH: Moorfields Eye Hospital; BEH: Bristol Eye Hospital; WEH: Western Eye Hospital; UCLH: University College London Hospital; MREH: Manchester Royal Eye Hospital; CAS: Clinical Activity Score.

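### The adjusted logistic model for the binary primary outcome puts about 17 parameters on about 25 expected failures, so ordinary maximum likelihood would exaggerate a real effect and moderately raise the type I error

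*Protocol article*

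**What the plan says.** Under Statistical analyses, the protocol article makes the two marginal comparisons (radiotherapy against sham, azathioprine against placebo) the primary intention-to-treat analyses. For the binary composite the model is logistic, "adjusting for minimisation variables, the factorial design, and the value of the outcome variable at baseline".

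Table 6, under Allocation of trial interventions, lists nine minimisation variables. Six have two categories, CAS and thyroid status have three each, and study centre has five ("MEH/BEH/WEH/UCLH/MREH"). Trial organisation allows further centres to be added.

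The sample size under Number of patients comes from a different, unadjusted analysis: "A two group continuity corrected chi-squared test with a 0.050 two-sided significance level will have 80% power" for success rates of 60% and 87%, "when the sample size in each group is 48". It concludes: "It is therefore necessary for there to be 96 subjects with complete final data sets".

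The article names no estimator for sparse binary data. The model remedies it does name are diagnostic plots and steps such as transforming continuous outcomes. Secondary analyses then add covariates that are imbalanced at baseline, and interaction terms, to the same models.

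**The concern.** Ordinary maximum-likelihood logistic regression relies on large-sample theory. When the rarer outcome supplies only one or two events per parameter, log odds ratios are biased away from zero and the usual Wald and likelihood-ratio tests reject too often. The sample size gives no reassurance here, because it was derived for a two-group chi-squared test with no covariates.

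The odds ratio, confidence interval and p-value for both interventions on the binary primary outcome would come from this model, and the article says that estimates and intervals will receive full attention. In a factorial trial one intervention may work and the other may not. The effect of the first would then be overstated, while the second would have a raised chance of a false positive.

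**Working it through.** **1. The plan's own figure.** Inputs from Number of patients: p1 = 0.60, p2 = 0.87, two-sided alpha 0.05, power 80%, continuity correction.

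- Mean rate = (0.60 + 0.87)/2 = 0.735.
- Uncorrected n = [1.960 × √(2 × 0.735 × 0.265) + 0.8416 × √(0.60 × 0.40 + 0.87 × 0.13)]² / 0.27² = (1.2233 + 0.5001)² / 0.0729 = 40.7, so 41 per group.
- Corrected n = (40.74/4) × [1 + √(1 + 4/(40.74 × 0.27))]² = 47.9, so 48 per group.
- Odds ratio = (0.87/0.13)/(0.60/0.40) = 4.46.

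The stated 48 per group and odds ratio of 4.462 are reproduced.

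**2. Model size.** From Table 6, entered as categorised: six two-level factors (6) + centre (4) + CAS (2) + thyroid status (2) = 14. Adding two treatment terms gives 16 covariates, and the intercept makes 17 parameters. A baseline-outcome term would make 18. Each further centre would add one.

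**3. Failures available.**

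- Planned rates: 48 × 0.40 + 48 × 0.13 = 19.2 + 6.24 = 25.4, and 25.4/17 = 1.5 per parameter.
- Neither treatment works (60% throughout): 96 × 0.40 = 38.4, and 38.4/17 = 2.3 per parameter.

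**4. What the model does with so few failures.** The document gives no covariate prevalences, so these are assumed. In the model comparisons below they were 25% to 50% for the two-level factors; 30/30/12/8/20% for the centres; 25/50/25% for the CAS bands; and 15/60/25% for thyroid status. Each simulated trial had 96 patients, 24 per cell, one effective treatment (true odds ratio 4.46) and one ineffective treatment. Covariates were not prognostic. Type I error refers to the ineffective treatment. There were 2,000 runs per model, except for the treatment-terms-only model, which used 4,000.

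| Model | Median OR (true 4.46) | Type I error, Wald | Type I error, likelihood ratio |
|---|---|---|---|
| Maximum likelihood, 17 parameters | 6.75 | 7.1% | 8.6% |
| Same, CAS scored linearly (16) | 6.57 | 7.3% | 8.5% |
| Same, centre omitted (13) | 5.82 | 6.4% | 7.1% |
| Maximum likelihood, 8 parameters | 5.10 | 5.7% | 6.5% |
| Maximum likelihood, treatment terms only | 4.63 | 4.6% | not run |
| Firth, full 17 parameters | 4.38 | not run | 4.7% (penalised) |

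The 17-parameter maximum-likelihood model in other settings, 4,000 runs each:

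- One treatment effective, covariates not prognostic: median odds ratio 6.57, type I error 7.0% (Wald) and 8.3% (likelihood ratio).
- One treatment effective, covariates moderately prognostic: median odds ratio 6.95, type I error 6.5% and 8.2%.
- Neither effective, about 38-39 failures: median odds ratio 0.98 to 1.02, type I error 6.6-7.2% and 7.4-8.1%.

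Further simulations of the same kind gave a median odds ratio of up to 7.0 and type I error up to 7.8% (Wald) and 8.9% (likelihood ratio). Firth medians there were 4.3 and 4.47. With patients allocated by minimisation the median odds ratio was 6.8 to 6.9. The mildest result with neither treatment effective was 5.9% (Wald) and 6.5% (likelihood ratio), from 2,000 runs. The Monte Carlo standard error near 7% is about 0.4 percentage points with 4,000 runs, from √(0.07 × 0.93/4,000), and about 0.6 with 2,000.

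**5. Relative size.** 6.6/4.46 = 1.48 and 7.0/4.46 = 1.57, so a real odds ratio is overstated by about half.

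**The case against.** - **Estimator and coding are not stated.** The article does not say ordinary maximum likelihood, fixed centre effects or categorised covariates, and an unseen analysis plan may name a penalised method or pool sparse centres. This is fair, and 17 is a count under one natural reading. But the adjustment set is fixed in the article. Scoring CAS linearly leaves the median at 6.57, and even leaving centre out altogether leaves it at 5.82.
- **The baseline term is unclear.** The composite is defined in Figure 4, which is not shown, so whether it has a baseline value cannot be known here. The count of 17 does not use that term.
- **The failure count depends on the scenario.** The figure of 25 belongs to the planned alternative. With no effect of either treatment there are about 38 failures and the type I excess is smaller, though still present.
- **Adjusted odds ratios are naturally further from 1.** This is true when covariates are prognostic. In the simulations, however, 4.46 was the conditional odds ratio itself, so the excess over it is small-sample bias.
- **Separation.** A reader might infer that the treatment odds ratio would often be infinite. Some coefficient diverged in about 15-20% of runs at 25-27 failures. Where this was broken down, a treatment coefficient diverged in only about 0.1%, so the problem lies almost entirely in nuisance terms.
- **Analysis should follow allocation.** A reader might infer that most minimisation variables should be dropped. The Firth results show that this is not needed.

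**Conclusion.** The point holds. The stated adjustment set, fitted by standard logistic regression at the planned size, gives an odds ratio about 1.5 times too large when a treatment truly has the planned effect. The type I error is about 7-9% instead of 5% in most settings examined. The bias in the odds ratio is the stronger part; the type I excess is moderate and varies with the failure count.

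Two stronger readings are not supported. The model does not create apparent benefit where there is none: with no true effect the median odds ratio stays at about 1. Nor is all the primary evidence compromised: the OI is also a primary outcome and is analysed by linear regression, as is CAS at 3 months, and these models are not affected in this way.

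The conclusion rests on assumed covariate prevalences, on Table 6 factors entered as fixed effects in roughly their listed categories, and on ordinary maximum likelihood as the default meaning of logistic regression.

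**What to change.** Keep the minimisation variables in the model. Add one sentence under Statistical analyses, before unmasking: the binary primary outcome will be fitted by Firth penalised logistic regression with the stated adjustment set, with penalised-likelihood tests and confidence intervals for both treatment terms, and ordinary maximum likelihood shown only as a sensitivity analysis.

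The change affects analysis wording only; sample size, conduct and the linear models stay as they are. The cost is slightly less familiar software and a less extreme reported odds ratio.

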## Background

Thyroid eye disease (TED) can be a visually disabling and cosmetically disfiguring condition which significantly impairs health-related quality of life [1-3]. A wide variety of immunosuppressive therapies have been used to target the early active inflammatory phase of the disease, including glucocorticoids (GC's), radiotherapy, antiproliferative agents, T-cell inhibitors and, more recently, biologics. The goal of these interventions is to suppress the autoimmune inflammatory phase of the disease, thereby altering the course of the disease and reducing the severity of residual changes in the extraocular muscles, orbital fat and other periocular soft tissues which result in permanent visual and cosmetic dysfunction [1,4,5].

GC's have been used to treat TED for over forty years, and several studies have demonstrated their efficacy with an overall response rate of 63–77% [1]. However, GC treatment is typically discontinued after 3 to 5 months [6-9] because of the side-effects associated with their long-term use, and subsequent disease recrudescence is a common problem [10]. This recurrence may be prevented by the concomitant use of ciclosporin [11] (which continues after GC treatment stops), and combinations of ciclosporin and prednisolone also achieve a better initial treatment response than either agent alone [6]. However, the routine use of such second-line immunosuppressive drugs in the management of TED has been limited by fears about their potential toxicity, and glucocorticoid monotherapy remains the mainstay of conventional treatment.

Radiotherapy is also well established in the treatment of TED [12,13], and its efficacy was affirmed in 1993 by the results of a prospective double-blind randomised control trial (RCT) which reported that orbital radiotherapy was as effective as oral prednisolone[7]. However, the same authors subsequently found that radiotherapy was no better than placebo (except in a subgroup of patients with motility impairment) [14], and a recent trial from the Mayo Clinic in the USA also could not demonstrate a beneficial therapeutic effect [15]. As a result, many clinicians, particularly in North America, have abandoned its use.

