4–7 days	60
1–2 weeks	40
3–6 weeks	30
7–10 weeks	20
11–14 weeks	15
15–18 weeks	10
19–20 weeks	7.5
21–22 weeks	5
23–24 week	2.5

**Table 3 T3:** Other Standardised Trial Treatments

Bisphosphonates	Risedronate sodium or alendronic acid
Proton pump inhibitors	Lansoprazole or omeprazole
Lubricants	Saline minims when required (no non-steroidal anti-inflammatory drops)

**Table 4 T4:** Trial timeline

**Week**	**-2**	**0**	**1–3**	**4**	**5–7**	**13**	**20**	**24**	**28**	**36**	**44**	**48**
**Orthoptic assessment**	✓	✓		✓		✓		✓		✓		✓
**Clinical assessment**	✓	✓		✓		✓		✓		✓		✓
**Blood tests**	✓	✓	✓	✓		✓	✓	✓	✓	✓	✓	✓
**Quality of life questionnaires**	✓					✓						✓
**Prednisolone**	start							stop				
**Azathioprine/Placebo**		start										
**Radiotherapy/Sham-radiotherapy**					✓							

Week -2 = enrolment; Week 0 = randomisation

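### Filling missing 12-month primary outcomes by last observation carried forward can bias the azathioprine comparison, by a modest amount in a direction that cannot be known in advance

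*Protocol article*

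**What the plan says.** Under Statistical analyses, the rule for the primary outcomes is: "Patients who have no outcome data for the primary analyses will have data imputed using last observation carried forward". No other method and no sensitivity analysis for missing data is stated. The same paragraph adds a measure to limit the problem: "Patients who have become non-compliant for any reason will still be invited to produce outcome data".

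Under Compliance and loss to follow-up, the forecast is that "10% of the azathioprine treated group will be intolerant of therapy or suffer an adverse event necessitating withdrawal from the trial", and that "5% will drop-out for other reasons".

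Table 4 uses the time scale "Week -2 = enrolment; Week 0 = randomisation". It places clinical assessments at weeks -2, 0, 4, 13, 24, 36 and 48 and the prednisolone stop at week 24. Both primary outcomes, the binary composite and the Ophthalmopathy Index (OI), are read at one year. On what follows when glucocorticoids are discontinued, the Background says that "subsequent disease recrudescence is a common problem".

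**The concern.** Carrying the last value forward assumes that a patient's state does not change after the last visit. The protocol gives a reason to doubt this. Every patient takes a tapering prednisolone course, and the primary endpoint falls about 24 weeks after it ends. A patient last seen at week 0, 4 or 13 was seen on steroid, and one last seen at week 24 was seen at about the end of the taper. Carrying such a value to week 48 leaves out the post-steroid course, and the azathioprine hypothesis is about long-term severity.

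If losses were equal in both arms, much of this error could cancel when there is no treatment effect. The protocol forecasts unequal losses, because azathioprine intolerance adds to one arm only. The rule also enters imputed values as if they had been observed, which makes confidence intervals too narrow.

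**Working it through.** **The plan's own figure.** Inputs from Trial size: 60% against 87% success, two-sided 5%, 80% power, continuity-corrected chi-squared test. The uncorrected size is [1.96·√(2·0.735·0.265) + 0.8416·√(0.60·0.40 + 0.87·0.13)]² / 0.27² = 40.7, so 41. With the correction, (40.7/4)·[1 + √(1 + 4/(40.7·0.27))]² = 47.9, so 48 per group. The stated 48 is reproduced. Exact power at 48 per group with the correction is 81.6%.

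**Forecast loss.**
- Azathioprine: 10% + 5% = 15%. Placebo: 5%. The ratio is 3.0. If the two risks are combined as 1 - 0.90·0.95, the figures are 14.5% and 2.9.
- Per margin of 48: 48·0.15 = 7.2 patients against 48·0.05 = 2.4.

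**Effect of the rule on the binary composite.** Let q be the success rate among carried-forward values and t the true 12-month rate. An arm's analysed rate is (1 - loss)·t + loss·q.

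*No true effect, t = 60% in both arms:*

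Difference = (0.85·0.60 + 0.15q) - (0.95·0.60 + 0.05q) = 0.10·(q - 0.60)

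| q | Source of q | Spurious difference (points) | Type I error, exact, uncorrected chi-squared |
|---|---|---|---|
| 0% | bound: all carried forward as failures | -6.0 | 9.3% |
| 63% | lower glucocorticoid response rate, Background | +0.3 | 4.9% |
| 77% | upper glucocorticoid response rate, Background | +1.7 | 5.3% |
| 100% | bound: all carried forward as successes | +4.0 | 6.9% |

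The middle rows use the Background's "overall response rate of 63–77" per cent. That rate is not defined on this trial's composite, so using it for q is an assumption.

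*True rates 87% against 60%, assumed to hold in the lost patients too:*

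Difference = (0.85·0.87 + 0.15q) - (0.95·0.60 + 0.05q) = 0.1695 + 0.10q

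At q = 63% this is 23.3 points and at q = 77% it is 24.7 points, against the planned 27. Exact continuity-corrected power at 48 per group is then 65% and 73%.

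**Precision.** The average loss is (15% + 5%)/2 = 10%, so 90 of 100 outcomes are observed and 100 are analysed. If the carried-forward values say nothing about the 12-month state, the reported standard error is √(90/100) = 0.949 of what it should be, or about 5% too small.

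**Timing.** Table 2 ends prednisolone 24 weeks after enrolment, which is week 22 from randomisation, while Table 4 marks the stop at week 24. The two tables should be reconciled. The argument here is the same on either.

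**The case against.** Several points on the other side are sound.

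- **Size.** With rates taken from the document, the shift under no effect is below 2 points and type I error stays near 5%. A reader might infer a distortion of about a fifth of the target effect (6/27 = 22%). That figure requires every lost patient to be carried forward as a failure, which is the opposite of carrying forward a steroid-improved state. It is a bound. The +4 bound likewise requires every carried-forward value to be a success.
- **Direction.** A reader might infer that the rule manufactures a benefit for azathioprine. That happens only if carried-forward success exceeds the lost patients' true success. Early departures carried forward as unimproved push the other way, and under the planned effect the rule dilutes the difference.
- **The dilution itself.** The 23 to 25 points assume that patients who left azathioprine would still have reached 87%. If they would not, part of the shrinkage is a genuine intention-to-treat effect. Nor would any other method recover all of the lost power.
- **The 3:1 ratio.** It is a planning forecast of withdrawal, not a count of missing outcomes. The invitation to non-compliant patients could narrow it. No adverse-event loss is forecast on placebo although everyone takes prednisolone, so 5% there may be low.
- **Scope.** A value from week 36 is off steroid. The Clinical Activity Score is read at 3 months, when all patients are scheduled to be on prednisolone, so the steroid argument does not reach it. Loss on the radiotherapy margin is expected to be balanced.
- **The replacement.** A missing-at-random model predicts those who left azathioprine largely from those who stayed, and can itself flatter azathioprine.

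These points limit the size and reach of the concern and shape the remedy. They do not make the stated rule sound: its bias has unknown sign, and none of the stated analyses would reveal it.

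**Conclusion.** The point holds for the two 12-month primary outcomes in the azathioprine comparison, for patients last seen up to about week 24. The rule is fixed in the text as the only stated handling, so it is not a detail left open.

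On the documents' rates, the shift in the composite under no effect is +0.3 to +1.7 points, within bounds of -6 to +4. Under the planned effect, 27 points become about 23 to 25 if the planned rates also hold in the lost patients. Standard errors are about 5% too small. These figures rest on the forecast 15% and 5% loss turning fully into missing outcomes, on the same q in both arms, and on borrowing q from the Background. The document does not support a claim that the rule favours azathioprine, or that it distorts the radiotherapy or 3-month activity comparisons in this way.

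The two statements on withdrawn and non-compliant patients also pull apart. One has intolerant patients leaving the trial; the other wants non-compliant patients to go on giving outcome data. The forecast wording does not prove that follow-up will stop, but the two need reconciling. Overall this should be fixed; it does not invalidate the design.

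**What to change.** 1. For the 12-month primary outcomes, replace last observation carried forward. Use a likelihood-based repeated-measures model for the OI over the scheduled assessments, and multiple imputation by arm from the serial assessments for the binary composite.
2. Keep last observation carried forward, and imputation of all missing outcomes as failure, as sensitivity analyses. Add one that departs from missing-at-random for patients who left azathioprine, since that is where the new method is weakest.
3. Reconcile Compliance and loss to follow-up with Statistical analyses, so that week-48 outcomes are sought from every randomised patient regardless of treatment status.

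The cost is revised wording and some programming before unmasking; the visits are already in Table 4. The drawback is that missing-at-random must be assumed and probed, and with about 7 expected losses on azathioprine the data will say little about that assumption. Item 3 therefore matters most, because an observed outcome needs no imputation.
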